#### Reporting urgent safety measures

The Sponsor or Investigator may take appropriate urgent safety measures (USMs) in order to protect the participant of a clinical trial against any immediate hazard to their health or safety without prior authorisation from the ethics committee. Where the researcher / practitioner takes urgent action that is not consistent with the protocol to prevent harm to a subject on a trial, they must immediately inform the Trial Manager and give full details of the measures taken and the decision-making process surrounding the action(s) taken. The Trial Manager will inform the CI, Sponsor and REC of these measures immediately, but no later than 3 days from the date the actions were taken. Written notification in the form of a substantial amendment is also required, which is anticipated within approximately 2 weeks of initial notification.

### Dissemination

Established dissemination practices will be adopted with a number of methods of disseminating the findings of the research to be used in order to ensure various target audiences receive feedback from the study. Results will be written up for a peer-reviewed publication in an academic journal. Additional publications will also be sought to reach a wide practitioner audience, rather than a single speciality publication. Findings will also be presented at national and international conferences and/or seminars to other mental health and forensic professionals. Throughout the study, a regular newsletter will be produced and made available to all prisoners and staff, which will summarise the current progress of the study and reinforce participation and support.

To feedback the results of the study to potential recipients of the new PROSPECT programme and other interested users of prison services, a series of presentations and seminars will be held with the local and national offender forums and agencies. We will collaborate with the ex-offender SURG group with such activities. Also, our collaborating charity partners have agreed to promote the study and its findings throughout the service user and offender communities. We shall also use our existing relationships with other prison charities to ensure the findings and implications of the study can be disseminated via forums and publications targeted at prisoner governors and policy makers. A summary of findings will also be forwarded to every prison governor in England and Wales.

Furthermore, as members of the Health and Justice Research Network (https://sites.manchester.ac.uk/hjrn/) with established links with HM Prison and Probation Service’s Safer Custody Group, we will be able to inform the development and delivery of psychological interventions for the prevention of suicide in prisons, both on a local and national level. We will also make recommendations to regulatory and advisory bodies, including NICE, British Psychological Society, and the Royal Colleges of Psychiatry and Nursing.

### Patient and Public Involvement (PPI)

The authors’ programme of prison suicide prevention research has been inspired and informed by several service users who identified an area of unmet need based on their own personal experiences. By working alongside people with lived experience, in a truly collaborative and open manner, we are confident this trial is grounded in the concerns of people who have experienced suicidal crises and distress whilst incarcerated in prison. The research team includes a service user and service user collaborators.

The PPI lead (DH), who has personal experience of suicidal distress and imprisonment, has been fundamental in the planning, decision making, design and development of this trial alongside fellow co-investigators. Working in partnership with the CI, the PPI lead has substantially been involved in carrying out extensive project development work, including reviewing relevant literature, investigation and evaluation of current service provision, advocating offender stakeholder views, and consolidating the formation of the project team to provide the necessary expertise for this research. Additionally, we were awarded a small grant from the Public Involvement Fund of the NIHR Research Design Service North West which enabled the research team to conduct two open events where an overview of the PROSPECT programme was presented to people with lived experiences of suicidality as prisoners. We have also consulted with our existing service-user reference groups that are associated with NIHR and MRC grants investigating suicide in mental health inpatients and people experiencing psychosis. These events and consultations have contributed advice and opinion on the aims, design and methods of the current protocol. One example of a specific change resulting from this work is the employment of a Service User Researcher within the study to help maximise recruitment and engagement of participants in this particularly sensitive mental health issue.

Furthermore, we are working with local and national offender health service user organisations to shape the research design, methods and processes to be adopted in the trial. Specifically, we are working with Revolving Doors to ensure continued consultation and active service user involvement throughout all stages of design and execution of the research development process. These collaborations have enabled us to establish our framework for the PROSPECT Service User Reference Group (SURG). The PROSPECT SURG comprises of reformed offender researchers and local ex-offenders with experience of prison healthcare services, and is chaired by our PPI lead. All members of the SURG will have personal experiences of suicidality within a prison setting, either directly themselves or as Samaritans trained ‘Listeners’ working within the prison. The SURG will lead on the public and patient involvement elements of the study and provide a forum for consultation throughout the duration of the trial.

As established within the feasibility trial, the SURG will be integral to the delivery of the proposed study and supported in maintaining active involvement in all stages of the project from jointly developing the work described in this application through to the recruitment, data interpretation, reporting, and dissemination. Specifically, the Service User Co-applicant will be invited to represent the SURG at all Programme Management Group meetings and members of the SURG will be routinely invited to attend the Programme Steering Committee. As is standard practice for our trials, the selection and writing of participant materials (information leaflets and consent forms, clinical materials, training materials, etc.) will be overseen and edited by the SURG. SURG members will also be influential in research and clinical staff training needs associated with the study and with providing an on-going focus on ethical matters concerning the emotional and practical needs of participants.

The SURG will also be actively involved in developing and delivering our dissemination strategy to ensure the outcomes of the trial are communicated in a manner that is inclusive and available to people who use prison healthcare services. Informed by our feasibility trial dissemination strategy, we will deliver a series of presentations and seminars held with offender forums and agencies, at a local and national level. We follow national guidelines on the involvement of the public in research and our payment procedures for SURG members’ contributions are in keeping with national recommendations (see www.invo.org.uk).

### Trial management

A Programme Steering Committee will be established and will comprise an independent chair, an experienced clinician, an independent statistician, and at least one service user representative with lived experience of the criminal justice system. The Chief Investigators (CI) will also attend the PSC accompanied by other senior study collaborators, where necessary. The PSC will oversee all aspects of the research including the trial and will make decisions on its continuation including the go/stop criteria for the internal pilot. The PSC will meet at least once per year.

An Independent Data Monitoring Committee (IDMC) will be established with all members to be independent as defined by NIHR research governance guidelines and should comprise of a clinician as chair, a further clinician and a mental health statistician. The IDMC will review serious adverse events considered by the CI to be research related and look at outcome data regularly during data collection. The Trial Statistician will attend the IDMC as appropriate. The Chief Investigators will only attend the IDMC when invited by the IDMC Chair. The IDMC will meet at least once per year.

The Programme Management Group (PMG) will consist of the Chief Investigator (DP), co-investigators, Programme/Trial Manager, and Trial Statistician and will consider day-to-day management issues and the overall progress of the trial. The PMG will meet on an at least monthly basis.

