Primary analysis of suicide ideation (BSSI) measured at 6 months (window 5–9 months) will use a linear mixed model with adjustment for baseline BSSI, stratification criteria and prognostic baseline covariates. The adjusted mean differences will be presented with 95% confidence intervals. BSSI is expected to be positively skewed and so the standard error and confidence interval for the treatment effect will be estimated by applying a bootstrap procedure [25] using the percentiles based on the results of 5000 replications (using the trial participant as the sampling unit). Primary analysis of suicidal behaviours (SB) measured within 6 months from randomisation will use a mixed model for count outcomes. The appropriate model with be chosen depending on the distribution of this variable. Analysis will adjust for baseline BS, stratification criteria and prognostic baseline covariates. The adjusted incident rate ratio will be presented with 95% confidence intervals. Due to the hierarchical ordering of these primary outcomes, no confirmatory claims can be made with regards to treatment benefit on SB unless it has first been demonstrated on BSSI. Secondary outcomes will be assessed using linear mixed models with similar adjustments. Analysis of primary and secondary outcome measures will be by intention to treat and will therefore include outcomes for all randomised participants in the group to which they were allocated, regardless of protocol adherence.

A therapeutic dose response model will be used to assess the effect of time engaged in therapy on treatment benefit. A complier average causal effect (CACE) model will be used to examine the treatment effect in those defined as ‘compliers’. Compliance will be defined from practitioner notes as a participant having started the ‘CBSP Phase’ of therapy. Treatment effect will be estimated within the subgroups defined by whether a participant has a history of suicide (Yes/No). As the study was not powered to investigate subgroup effects, this will be a purely exploratory analysis. All inferential analyses will adjust for stratification factors used in randomisation. Additionally, baseline outcome and prognostic variables will be adjusted for to improve power. Where outcome variables are skewed, bootstrapped confidence intervals will be presented. There will be no interim analysis of outcome data during the trial.

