## Discussion

### Strategies to improve and monitor treatment adherence

The PROSPECT programme will be delivered by accredited Psychological Practitioners (e.g. BABCP accredited Psychological Practitioners or HCPC registered Clinical/Forensic/Counselling Psychologists) with one practitioner allocated to each of the four prisons in the intervention arm of the trial. Trial Therapists / practitioners will already be well trained in delivering psychological therapies, but they will also undergo an intensive training period to gain familiarity with the specifics of the PROSPECT programme, led by the programme team members. The training will involve a combination of interactive lectures and seminars, modelling, role-plays, reading assignments, and homework exercises, which will be delivered by the Chief Investigator (DP) who has extensive training and several years of experience with the CBSP intervention. We anticipate this training will be delivered once at the outset of the trial, although individual training will also be delivered for any replacement practitioners who join the trial at a later date. During the trial, practitioners will receive fortnightly supervision from the Chief Investigator (DP) and other experienced Clinical Psychologists familiar with the treatment protocol. Teleconferencing technologies will be used to ensure practitioners working in both the Northwest and Yorkshire regions can access clinical supervision. Supervision will focus on individual client work, techniques delivered by the therapist, intervention planning and problem-solving any barriers to implementation. Adherence will be monitored throughout the intervention delivery period using a structured therapy delivery diary.

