#### Serious Adverse Events (SAEs)

All SAEs occurring from the time of consent until 1 month after the final follow-up assessment completion will be recorded on the SAE report form and emailed to the Prospect Trial Manager and CI (as sponsor’s representative) immediately and within 24 h of the research staff becoming aware of the event. Any change of condition or other follow-up information will be reported to the Trial Manager and CI as soon as it is available, or at least within 24 h of the information becoming available. Events will be followed up until the event has resolved or a final outcome has been reached.

The Trial Manager and CI will review the SAE form. If the SAE is related to participation in the trial, the CI will review the expectedness in relation to the nature or severity of which is not consistent with the effects or consequences of participation in a psychological intervention trial. All adverse events that are research related will be reported by the CI to the relevant host prison responsible clinical team and the Data Monitoring and Ethics Committee (DMEC) on a regular basis and in an expedited fashion. Fatal or life-threatening events will be reported to the Programme Steering Committee, the DMEC and the relevant Ethics Committee within seven days of knowledge of such cases.

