#### Monitoring of adverse events

Due to the nature of the participant sample, it is anticipated that a number of suicide-related adverse events (expression of suicidal ideation, intent, behaviours and attempts) will occur in both the active and control arms of the research trial. As stated, suicidal behaviour is one of the primary outcome measures of this study. However, should the IDMC become aware of an inflated rate of suicide-related adverse events in the active, relative to the control, arm of the trial that is attributable to participation in the trial, then the PSC may be alerted to consider recommending a premature discontinuation of the trial (Duggan et al., 2014).

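### The IDMC is expected to notice an active-arm excess of suicide-related events, but fatal or life-threatening events apart, its stated safety feed first passes the chief investigator's relatedness judgement; its look at outcome data is also not reconciled with the bar on interim analysis

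*Protocol article*

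**What the plan says.** All references are to the protocol article.

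- **Monitoring of adverse events.** Suicide-related events are expected in both arms. The check is comparative: "should the IDMC become aware of an inflated rate of suicide-related adverse events in the active, relative to the control, arm of the trial" and the excess is one "that is attributable to participation in the trial, then the PSC may be alerted to consider recommending a premature discontinuation of the trial".
- **Trial management.** The committee's remit: "The IDMC will review serious adverse events considered by the CI to be research related and look at outcome data regularly during data collection". It meets at least once a year.
- **Serious Adverse Events (SAEs).** All SAEs go to the Trial Manager and the CI. What then goes to the committee, here called the DMEC, is narrower: "All adverse events that are research related will be reported by the CI". A separate route carries no stated relatedness condition: "Fatal or life-threatening events will be reported to the Programme Steering Committee, the DMEC and the relevant Ethics Committee within seven days".
- **Adverse Events (AEs).** Self-harm, suicidal behaviour and ideation are recorded for participants from consent until one month after the final follow-up assessment.
- **Strategies to improve and monitor treatment adherence.** The CI delivers the practitioner training, and "practitioners will receive fortnightly supervision from the Chief Investigator" together with other experienced clinical psychologists. Supervision covers individual client work.
- **Data analyses of the RCT.** "There will be no interim analysis of outcome data during the trial".

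**The concern.** A check for excess events in one arm needs the events of both arms, counted by the same rule, whatever anyone thinks caused each one. The stated routing places a case-by-case relatedness judgement ahead of that comparison. The judgement belongs to someone who trained the practitioners and discusses their cases, and who therefore cannot be assumed blind. In suicidal prisoners, where such events are expected with or without the therapy, a single event is hard to attribute. An excess between randomised arms is the evidence that can be attributed, and the filter may remove it.

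The second issue is separate. One section has the committee look at outcome data regularly, and another rules out interim analysis of outcome data. Suicidal behaviour is both a recorded adverse event and a co-primary outcome, so safety review and an efficacy look can be the same table. A reader cannot tell whether comparative outcome data will be seen before the final analysis, or for what purpose.

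**Working it through.** The protocol states no figure on this point, so there is nothing to reproduce. The check sets the sections side by side.

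**1. What is recorded.** All SAEs, and all listed suicide-related AEs, in both arms, from consent to one month after final follow-up (the sections on AEs and SAEs). The data for a full comparison therefore exist.

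**2. What is stated to reach the committee.**
- SAEs the CI considers research-related (Trial management): filtered.
- All research-related AEs, serious or not, reported by the CI (Serious Adverse Events): filtered.
- Fatal or life-threatening events, within seven days (Serious Adverse Events): no filter stated.
- Outcome data, looked at regularly (Trial management): no relatedness filter, but content and layout are not stated.

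No section says that all suicide-related events go to the committee by arm regardless of relatedness.

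**3. What the filter does to the comparison.** Let p_A and p_C be the true event risks in the active and control arms, and s_A and s_C the shares of events judged research-related. The check needs p_A − p_C, or p_A/p_C. The filtered feed shows s_A·p_A − s_C·p_C, or (p_A/p_C)·(s_A/s_C).
- If both shares equal s, the difference shrinks to s·(p_A − p_C), on fewer events.
- If the shares differ, the ratio is multiplied by s_A/s_C, which reflects classification and not harm.

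The documents give neither the risks nor the shares, so no size can be put on either effect.

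**4. Does the attribution wording resolve this?** The trigger concerns an excess attributable to participation in the trial. That describes a property of the excess, which is judged after comparing arms. Screening single events for relatedness beforehand is a different step and does not supply the comparison.

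**5. Does the outcome data fill the gap?** In part. Suicidal behaviour is a co-primary outcome, collected in both arms with the same interview by researchers intended to be blind. It is obtained at the 6-month assessment, for which the allowed window is 5–9 months. A participant's events therefore enter the outcome data only about 5 months or more after randomisation. They do not enter at all for those not interviewed, and planned attrition is up to 30%.

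**6. Outcome look against the interim bar.** With 21 months of recruitment and 6 months of follow-up, 21 + 6 = 27 months. At least yearly meetings then imply about two or more looks. The two statements are compatible if the looks are pooled, limited to data quality, or by arm for safety with no efficacy test. They conflict if the looks compare arms on efficacy. The text does not say which applies.

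**7. Name of the body.** The SAE section says DMEC; the sections on monitoring and trial management say IDMC. The abbreviations list contains only IDMC. They are treated here as one body, which the sponsor should confirm.

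**The case against.** The strongest defence is that the committee has more than one source. It receives non-serious related events and fatal or life-threatening events. It may see suicidal behaviour from both arms in the outcome data, and the phrase about becoming aware does not restrict where the information comes from. This stands, and a reader who infers that the IDMC sees only serious events judged related would be wrong.

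Four further inferences are tempting and are not supported:

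- **That control-arm events could almost never be judged related.** The test is relation to research participation, not to the therapy alone. Control participants also complete assessments that may cause distress and receive enhanced monitoring.
- **That this is the only safety check, or that it cannot work.** The article also has withdrawal-consideration criteria, a distress protocol with risk assessment at each interview, and urgent safety measures.
- **That detection is unequal between arms by some known amount.** The therapy arm has up to 20 sessions in which events may surface. But both arms have enhanced monitoring, records may be accessed with consent, and the figures showing contact timing are not available. No detection rates are given. What remains is a reason to show the source of each report.
- **That the final 5% test is inflated.** No efficacy test or efficacy stopping rule is attached to the looks. If outcomes were tested by arm at an unadjusted two-sided 0.05 at each of 2 to 4 equally spaced looks, simulation puts the overall error at about 0.083 to 0.126. If nothing is tested and no efficacy stop follows, there is no inflation.

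It can also be said that table layouts belong in a committee charter. That is fair for layouts. It does not cover a stated routing rule that works against a stated check, or two sections that read differently on outcome looks.

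**Conclusion.** The point holds as a conflict between stated rules. The between-arm harm check relies on a comparison that the stated safety feed does not provide for. Fatal or life-threatening events apart, that feed is filtered by the CI's relatedness judgement before any independent comparison, and the CI is close to the intervention. The filter can hide an excess, and the outcome data offset this only partly and late.

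The regular look at outcome data and the bar on interim analysis are unreconciled but not irreconcilable.

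No size can be given: it depends on the share of events judged related in each arm, which the documents do not state. The conclusion assumes that DMEC and IDMC are the same body and that no unshown charter already sends unfiltered by-arm listings. It does not bear on the sample size, the outcomes or the treatment.

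**What to change.** Reconcile the four sections (Data analyses of the RCT, Serious Adverse Events, Monitoring of adverse events, Trial management) as follows:

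1. State that at each meeting the IDMC receives all SAEs and all recorded suicide-related AEs by arm, regardless of the CI's relatedness judgement. The CI's view can be shown as a column, not used as a filter.
2. Show the source of each report, so that events reported by practitioners can be read separately from those found through sources common to both arms.
3. State that the committee's look at outcome data is for safety and data quality, with no efficacy test. If a comparative efficacy look is intended, declare it an interim analysis and amend the statement that there will be none.
4. Confirm that the DMEC and the IDMC are one body, and use one name.

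The cost is protocol and charter wording plus one by-arm listing from data already being recorded. No new data collection is needed.
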